## Abstract

**Background:**

The many improvements in cancer therapies have led to an increased number of survivors, which comes with a greater risk of consequent/subsequent cardiovascular disease. Identifying effective management strategies that can mitigate this risk of cardiovascular complications is vital. Therefore, developing computer-driven and personalized clinical decision aid interventions that can provide early detection of patients at risk, stratify that risk, and recommend specific cardio-oncology management guidelines and expert consensus recommendations is critically important.

**Objectives:**

To assess the feasibility, acceptability, and utility of the use of an artificial intelligence (AI)-powered clinical decision aid tool in shared decision making between the cancer survivor patient and the cardiologist regarding prevention of cardiovascular disease.

**Design:**

This is a single-center, double-arm, open-label, randomized interventional feasibility study. Our cardio-oncology cohort of > 4000 individuals from our Clinical Research Data Warehouse will be queried to identify at least 200 adult cancer survivors who meet the eligibility criteria. Study participants will be randomized into either the Clinical Decision Aid Group (where patients will use the clinical decision aid in addition to current practice) or the Control Group (current practice). The primary endpoint of this study is to assess for each patient encounter whether cardiovascular medications and imaging pursued were consistent with current medical society recommendations. Additionally, the perceptions of using the clinical decision tool will be evaluated based on patient and physician feedback through surveys and focus groups.

**Summary:**

This trial will determine whether a clinical decision aid tool improves cancer survivors’ medication use and imaging surveillance recommendations aligned with current medical guidelines.

**Trial registration:**

ClinicalTrials.Gov Identifier: NCT05377320

## Introduction

Cardiovascular disease is a leading cause of death in cancer patients, second only to the development of recurrent or secondary cancer. Approximately two million new cancer diagnoses and > 600,000 new cancer deaths are estimated to occur each year [1]. Nearly 17 million Americans are cancer survivors, and this number is expected to increase to more than 22 million by 2030 [2, 3]. Of these 17 million survivors, four million have had breast cancer, which is often the most common cancer with treatment leading to cardiovascular complications in cardio-oncology clinics [3–9]. Improvement in cancer therapies has increased the number of patients surviving cancer, and often confer increased cardiovascular disease risk. Moreover, specific cancer therapeutic strategies have cardiovascular toxic effects, including those that employ anthracyclines and HER2 inhibitors [10]. Given the growing numbers in cancer survivors and their increased susceptibility to cardiovascular disease, a clinical decision aid intervention that classifies cancer patients most inclined to develop cardiovascular disease and identifies effective treatment strategies that mitigate cardiovascular disease progression is urgently needed.

Many cardiologists are not specifically trained to care for cancer patients and have limited familiarity with cardio-oncology recommendations [6, 11–17]. Furthermore, management and follow-up of cardiovascular risk for cardio-oncology patients and survivors often differ from that of individuals in the general population with similar cardiovascular risk factors. For example, breast cancer patients at risk for cardiovascular complications are often insufficiently treated with cardioprotective medications and appropriate frequencies of cardiac surveillance imaging [18–20]. Several cardio-oncology guidelines, medical society scientific statements, and consensus recommendations have become available in recent years [21–28]. Yet, we are challenged with how best to support physicians and cancer survivors to implement these recommendations, especially those at highest risk for developing cardiovascular disease. The relative absence of training in cardio-oncology has therefore resulted in a tremendous knowledge gap in optimal patient care [11–15].

A clinical decision aid powered by artificial intelligence capable of appropriately evaluating and assessing cardiovascular disease risk with evidence-based suggestions for care for cancer survivors may help bridge this gap. Notably, artificial intelligence algorithms trained on 20-year follow-up data for > 4,000 racially diverse survivors of various cancers were recently developed and validated. The algorithms use cardiovascular imaging (echocardiograms) and clinical variables and can predict cardiovascular disease events [29]. Further, some of these machine learning and network algorithms have been used to precisely predict cardiac risk assessment in a database study, by analyzing how similar various patients are to each other [29] (Fig. 1). In general, such “patient similarity” machine learning and network algorithms represent each patient as a combined vector of features and characteristics, and the similarity between two patients can be measured by a variety of distance measures. In the absence of substantial missing data, the algorithms can be used to form clusters or groups of patients to further facilitate prediction and classification. However, none of these algorithms have yet been incorporated into a clinical decision aid or used in clinical practice for cardio-oncology patients.

**Fig. 1 Fig1:**
[figure not shown]
Patient Similarity Machine Learning and Network Analysis. **A** Area under receiver operator curve (AUROC; AUC) for prediction of cardiovascular diseases after cancer (Ca) diagnosis in > 4000 patients. **B** Patients most similar to each other are closest to each other and form clusters in networks; patients in the same cluster or similarity network tend to display similar rates of cardiovascular disease (CVD) and mortality. **C** Cumulative hazard of new (or de novo) CVD after cancer diagnosis; cardiovascular disease risk clusters (C1-C4) based on the patient similarity machine learning and network analysis. Used with permission [29]

This trial design manuscript describes our study, in which these machine learning algorithms will be incorporated into a clinical decision aid and used in clinical practice for cardio-oncology patients. In a cohort of cancer survivors, we propose to evaluate the feasibility of this novel clinical decision aid with the expectation that it will ultimately improve medication use and imaging utilization to mitigate cardiovascular risk. For this feasibility study, we will create the clinical decision aid and test the central hypothesis that this novel clinical decision aid accessed via the electronic health record will be acceptable to both cancer survivors and their cardiologists, and will favorably impact appropriate medication use and cardiac imaging surveillance.

## Methods

### Study design

This is a single-center, double-arm, open-label, randomized interventional feasibility study that will determine whether a novel clinical decision aid accessed via the electronic health record will be acceptable to both cancer survivors (Table 1) and their cardiologists. In the study, we will assess whether use of the tool in shared decision-making favorably impacts appropriate medication use and cardiac imaging surveillance (Table 2). The overall process for this study is as follows. Cardiovascular risk assessment will begin with the artificial intelligence algorithm based on clinical, laboratory, and echocardiographic data (Table 3). The artificial intelligence algorithms used are explainable. A separate rules-based algorithm based on existing guidelines, expert recommendations, and medical society scientific statements has also been created (Brown et al., in review) (Fig. 2), and this tool will also be leveraged as a component of this feasibility clinical trial. Cardiovascular risk information from the artificial intelligence algorithm output will be placed alongside evidence-based suggestions for the patient’s care from the rules-based algorithm. The cardiovascular risk information and the evidence-based suggestions will be visually displayed side-by-side; this is the clinical decision aid, which is one of the most novel parts of this trial. Clinicians will meet with each patient and use the clinical decision aid to make recommendations for management based on these results plus their own judgement, taking into account each patient’s individual characteristics. Each patient will collaboratively decide with their clinician whether they will follow the medication use and imaging surveillance suggestions based on existing guidelines, expert recommendations, and medical society scientific statements will be created. We will then assess differences in medication use and imaging surveillance consistent with national guidelines and recommendations, as well as perceptions of the tool using surveys and focus groups.

**Table 1 Tab1:** Patient baseline characteristics

*Sociodemographic Characteristics*	*Geocoding*
Age	County
Race	State
Sex	Zip
Marital status	
Employment status	
Ethnicity	
Language	
*Cardiovascular Conditions/Comorbidities*	*Tumor Characteristics*
Atrial Fibrillation	Diagnosis
Coronary Artery Disease	Site
Cardiomegaly	Type
Cardiomyopathy	Histology
Diabetes	Behavior
Hyperlipidemia	Stage
Heart Failure	Grade
Myocardial Infarction	Metastasis
Peripheral Artery Disease	Surgical margins
Stroke	
*Major Cardiovascular Medication Classes*	*Cancer Medication Classes*
ACE Inhibitors	Antineoplastic Antibiotics (anthracyclines)
Antianginals	Antineoplastic Enzyme Inhibitors
Angiotensin II Receptor Antagonists	Antineoplastic—Antibodies
Beta Blockers	Antineoplastic—Anti-HER2 Agents
Alpha–Beta Blockers	Antineoplastic—Angiogenesis Inhibitors
Alpha 2 Inhibitors	Antineoplastic—EGFR Inhibitors
Calcium Channel Blockers	Mitotic Inhibitors
Diuretics	Antineoplastic—Hormonal and Related Agents
Antihyperlipidemics	Antineoplastic—Immunomodulators
Antihypertensives	Chemotherapy Adjuncts
Antiarrhythmic	Antineoplastic—PDGFR-alpha Inhibitors
Anticoagulants	Antineoplastic—Hedgehog Pathway Inhibitors
Vasopressors	Antineoplastic—Cellular Immunotherapy
Mineralocorticoids	Alkylating agents
Phosphodiesterase Inhibitors	
Direct Renin Inhibitors	
Antidiabetic	

*ACE* Angiotensin-converting enzyme, *EGFR* Epidermal growth factor receptor, *HER2* Human epidermal growth factor receptor 2, *PDGFR* Platelet-derived growth factor receptor

**Table 2 Tab2:** Patient outcomes/endpoints

**Primary Outcomes/Endpoints**
***Cardiovascular Imaging Recently Obtained***
*Cardiac Magnetic Resonance Imaging*
*Coronary Calcium Scan*
*Coronary Computed Tomography Angiography*
*Electrocardiogram ordered*
*Transthoracic echocardiogram*
***Cardiovascular Imaging Ordered***
*Cardiac Magnetic Resonance Imaging*
*Coronary Calcium Scan*
*Coronary Computed Tomography Angiography*
*Electrocardiogram ordered*
*Transthoracic echocardiogram ordered*
***Pre-Existing Cardiovascular-Related Medications***
*Patient already on ACE Inhibitor*
*Patient already on ARB*
*Patient already on Beta Blocker*
*Patient already on Statin*
*Patient already on Other Cardiovascular Medications*
*Patient already on Antidiabetic Medication*
***Cardiovascular-Related Medications Ordered***
*Prescription of ACE Inhibitor*
*Prescription of ARB*
*Prescription of Beta Blocker*
*Prescription of Statin*
*Prescription of Other Cardiovascular Medications*
*Prescription of Antidiabetic Medication*
**Secondary Outcomes/Endpoints**
*Survey Results*
*Focus Group Findings*
*Relevant Lab Testing Recently Obtained*
*Relevant Lab Testing Obtained*

*ACE* Angiotensin-converting enzyme, *ARB* Angiotensin receptor blocker

**Table 3 Tab3:** Algorithm variables in the study. Used with permission [29]

Lab test (including demographic)	Echocardiographic
Sex	LVEF (left ventricular ejection fraction)
Race	Heart rate
Family history	BSA (body surface area)
Tobacco use	SBP (systolic blood pressure)
Alcohol use	DBP (diastolic blood pressure)
Diabetes	EDV (end-diastolic volume)
Hypertension	ESV (end-systolic volume)
Hyperlipidemia	LVEDVi (left ventricular end-diastolic volume index)
Peripheral edema	LVESVi (left ventricular end-systolic volume index)
Orthopnea	
Chest pain	
Shortness of breath	
Fatigue	
Age	
BMI (body mass index)	
eGFR (estimated glomerular filtration rate)	
RBC (red blood cell)	
Hematocrit	
MCHC (mean corpuscular hemoglobin concentration)	
MCV (mean corpuscular volume)	
MCH (mean corpuscular hemoglobin)	
Blood glucose	
Calcium	
Total protein	
Sodium	
Potassium	
Chloride	
Carbon dioxide	
WBC (white blood cell)	
Platelet	
Creatinine	
ALT (alanine aminotransferase)	
AST (aspartate aminotransferase)	
Albumin	
ALP (alkaline phosphatase)	
Bilirubin

**Fig. 2 Fig2:**
[figure not shown]
Clinical Decision Aid Incorporates Artificial Intelligence and Rules-Based Algorithms for Risk Prediction (Artificial Intelligence-Powered Personalization) and Guidelines Implementation (Rules-Based Personalization). Templates from Infograpia were used in the making of this graphic

Prior to implementing this protocol, the protocol, informed consent form, health insurance portability and accountability act authorization and any other information pertaining to participants will be approved by the Medical College of Wisconsin institutional review board.

### Study population

The overall study cohort dataset of > 4,000 individuals includes demographic, physiological, laboratory, medication, medical history, and outcomes data relevant to cardiovascular risk stratification in individuals with a history of cancer, as well as cardiovascular imaging reports [30]. This cohort will be queried to identify ≥ 200 adult cancer survivors (including ethnic/racial minorities) clinically considered to be at intermediate, high, or very high cardiovascular risk following cancer therapy determined imprecisely based on demographic and comorbidity information [3, 11, 31–34].

### Recruitment & randomization

From among these same ≥ 200 patients, our team will partner with the patients’ primary care providers (PCPs), hematologists, or oncologists to recruit and consent 200 adult cancer survivors for clinic visits and focus groups for the remainder of the study. The study team members will contact each potential patient to gauge their interest to participate in the study. Potential study participants who exhibit interest and/or agree to enroll in the study will be provided an information packet containing an informed consent form that offers a more in-depth description of the study and contact information if they are to have additional questions. Those who do not express interest in the study will be noted and no longer contacted. Study participants will be randomly distributed into either the Clinical Decision Aid Group (where *N* = 100 patients will use the clinical decision aid in addition to current practice) or the Control Group (where *N* = 100 patients will only have access to current practice) based on the following stratification factors: sex and race/ethnicity. In collaboration with our biostatistician, patients will be randomly distributed into one of these two arms based on the following stratification factors: sex (2: male, female) and race/ethnicity (3: White, Black, other).

### Clinical visits and clinical decision aid intervention

Patients in the study will meet with study cardiologists in either a virtual or in-person clinically indicated visit, with technical support and training provided by the study team as needed. For those in the Clinical Decision Aid Group, their personalized risk output from the artificial intelligence algorithms will be organized in a meaningful and user-friendly way, using customized pictographs visually representing personalized and precise patient risk in the clinical decision aid (Fig. 3). This will be juxtaposed with suggestions for medication use and imaging based on existing guidelines, expert recommendations, and society scientific statements (from Fig. 2).

**Fig. 3 Fig3:**
[figure not shown]
Artificial Intelligence-Powered Clinical Decision Aid Mockup. The visual interface will continually be iterated and improved based on patient and clinician feedback during the study and beyond; additional components of the mockup illustrate the explainability and transparency of the algorithms and models employed in the clinical decision aid

The clinical decision aid will be made available via a simple web-based interface hosted online at the Cardiology Oncology Innovation Network (CardioOncCOIN.Org). A link to the clinical decision aid webpage interface will be placed in each patient’s electronic health record. Study physicians can click on this link in the patient’s chart to access the webpage. In this way, the webpage interface will be independent of the particular electronic health record. We will also initiate efforts to have the same clinical decision aid integrated into Epic via the Epic App Orchard. If we are able to achieve this, then the study physician will also be able to access the clinical decision aid in this way.

In both study arms, video and audio may be recorded throughout the clinical visit for use in subsequent objective analysis of shared decision-making, the collaborative process by which health care choices are made by the patient with guidance from a health care professional [35]. Shared decision-making will be scored by study staff using the OPTION5 scale [36–38]. Study participants will be asked to complete established Likert scale surveys that reflect their personal health perceptions, decisions, and behaviors.

### Focus groups

As part of an exploratory study, a total of 20 patients in the Clinical Decision Aid Group and all the study physicians will attend two patient or physician focus group sessions, respectively. The focus groups will discuss the virtual clinical decision aid interface and how to improve it. Treating physicians will meet separately from patients in their own focus groups. The first will be held a week after the initial visit and the second held a week after a clinically indicated follow-up visit when applicable. Focus groups will be run by our qualitative research collaborators who will facilitate discussions about the user experience, to obtain critical feedback on the virtual clinical decision aid interface. The expectations for these focus group sessions are to help our study team further develop and improve the clinical decision aid interface to fit the needs of patients and their clinicians.

### Follow-up clinic visits

Follow-up clinic visits may be pursued as clinically indicated. Patients in the Clinical Decision Aid Group may again use the clinical decision aid, which would be an updated version incorporating some of the focus group feedback and suggestions. In addition, study participants in the Control Group will receive their risk group information at the end of the study if desired and can review again at that time with their clinicians the preventive steps they have taken for heart health.

### Primary endpoints

Chart reviews will also be completed for all patients to assess medication use and imaging patterns in accordance with cardio-oncology recommendations at three and six months after the baseline clinic visit, as the primary endpoints.

If the patient chooses not to or is unable to pursue the recommendations suggested by the clinical decision aid as discussed by the physician, this would be noted in the chart. Therefore, if the physician offers the recommendation, this will be considered consistent with the society statements, even if the patient chooses not to follow the recommendation. An adjudication committee of 3 people may be established to decide what is considered consistent with evidence-based recommendations. If 2 of 3 people agree, that would be considered consistent with evidence-based recommendations.

Success will be determined by ≥ 85% of clinic visits using the clinical decision aid resulting in pursuit of medication use and cardiac imaging surveillance patterns commensurate with recommendations specific to cancer survivors, with overall rates the same or higher than the group without the clinical decision aid, as well as overall favorable patient and physician focus group comments and survey responses.

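### The primary endpoint rests on chart judgement that can reveal the arm, with optional adjudication and a 2-of-3 rule that has no route to an inconsistent rating

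*Protocol article*

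**What the plan says.** The Study design section states: "This is a single-center, double-arm, open-label, randomized interventional feasibility study". The Primary endpoints section says how the outcome is obtained: "Chart reviews will also be completed for all patients to assess medication use and imaging patterns in accordance with cardio-oncology recommendations". This is done twice, three and six months from baseline. The reference standard is a body of guidelines, expert recommendations and society scientific statements.

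The same section covers advice that is not followed. If the patient does not or cannot pursue "recommendations suggested by the clinical decision aid as discussed by the physician, this would be noted in the chart". It continues: "Therefore, if the physician offers the recommendation, this will be considered consistent with the society statements", whether or not the patient accepts.

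On adjudication it says "An adjudication committee of 3 people may be established to decide what is considered consistent with evidence-based recommendations" and then "If 2 of 3 people agree, that would be considered consistent with evidence-based recommendations". The article does not say when the committee would set its criteria, which charts it would see, or whether reviewers or members would be masked to arm.

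The section on clinical visits and the intervention adds: "A link to the clinical decision aid webpage interface will be placed in each patient’s electronic health record".

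Success has three parts: at least 85% of aid visits consistent, an overall rate no lower than control, and favourable feedback. Separately, the Data analysis section sets significance at P < 0.05.

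**The concern.** Matching a patient's orders to several guidelines and statements takes judgement, and providing for a committee concedes this. If the person judging can see the arm, borderline charts may be read more generously in one arm than in the other. Three features of the text leave room for that.

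- **The chart can reveal the arm.** A note about a recommendation suggested by the aid can arise only where the aid was used.
- **The documentation rule is described on one side only.** A physician's offer scores as consistent, but the note that records a declined offer is described only for aid-suggested recommendations. Nothing parallel is stated for control, so an undocumented control offer could be scored inconsistent.
- **The adjudication is loose.** It is optional, its standard has no stated date, and the voting sentence has no route to an inconsistent rating.

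At stake are the between-arm comparison and the clause requiring the aid arm to be no worse than control. Both rest on this classification.

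**Working it through.** **1. The plan's own figure.** Inputs from Sample size and power analysis are 40% against 60% and 80% power. Two-sided alpha of 0.05 is assumed, because sidedness is not stated. With the pooled-variance formula,

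n = [1.960·√(2·p̄(1−p̄)) + 0.842·√(p1(1−p1)+p2(1−p2))]² / (p2−p1)², where p̄ = 0.50,

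n = 96.9, so 97 per group. For 40% against 85% it gives 16.9, so 17 per group. Both stated figures reproduce. The point below disputes no sample size.

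**2. The voting sentence.** Three yes/no votes have 2³ = 8 patterns. In all 8, at least two members agree with each other. Read literally, the sentence would therefore class every case as consistent, including a unanimous vote that it is not.

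**3. Effect of one-sided leniency.** Inputs are 100 patients per arm and 40% consistency (both from the article), taken as the true rate in both arms. The assumption, which is not in the article, is that a fraction f of truly inconsistent aid-arm charts is scored consistent and none in control. Then

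observed aid rate = 0.40 + 0.60·f.

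Results come from exact enumeration of two independent binomials, with a pooled two-proportion z-test at two-sided 0.05. The last column treats 100 visits as 100 patients.

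| f | Observed aid rate | Significant in favour of aid | Aid rate at least equal to control | Aid rate reaches 85% |
|---|---|---|---|---|
| 0 | 40% | 2.6% | 53% | below 1e-11 |
| 10% | 46% | 14.2% | 82% | below 1e-11 |
| 20% | 52% | 41.6% | 96% | below 1e-11 |

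**4. Two reference points.** To move a true 40% to 85% by leniency alone needs f = (0.85−0.40)/0.60 = 75%. To imitate the planned 40% to 60% effect needs f = 0.20/0.60 = one in three.

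**5. Equal leniency.** If 10% or 20% were upgraded in both arms alike, the chance of significance in the aid's favour stays near 2.8%. The harm comes from a difference between arms, not from leniency as such.

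**The case against.** The strongest reply is that much of this reads silence as a defect. A reader might infer that reviewers will be unmasked and that the standard will be set after the orders have been seen. The article says neither. An open-label trial can still have masked outcome review, a journal article often leaves such detail to the full protocol, and deciding what is consistent may mean agreeing criteria beforehand. That stands: the text supports only that masking is not described and that the timing is open.

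A reader might also take the aid link as showing the arm. The link goes into each patient's record with no arm named, so it need not separate the arms. The notes on aid suggestions are the evidence that does.

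The voting sentence follows directly on the committee's task, and it almost certainly means that two of three rate the care consistent. It is a drafting slip, not a rule anyone would apply literally.

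Table 2 lists recorded orders and prescriptions, so the raw facts are not soft. Judging whether they match the recommendations still is.

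Finally, the upgrade rates have no source in the article, and the study calls itself a feasibility study. Both are fair. However, the Abstract's summary says the trial will determine whether the aid improves guideline-aligned care, and the sample size section addresses that comparison. What the reply does not remove is what the text itself fixes: arm-revealing notes in the chart to be reviewed, a scoring rule whose documentation is described for aid-suggested advice only, and an optional committee.

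**Conclusion.** The concern holds in limited form. As written, the plan permits differential misclassification in favour of the aid. It does not show that this will happen.

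Under the assumed one-sided upgrading of 10% or 20%, with no true effect, the chance of a significant result favouring the aid goes from about 2.6% to 14% or 42%. At 10%, the chance of meeting the no-lower-than-control clause goes from 53% to 82%. A reader might infer that the whole success rule is exposed in the same way. It is not: at these rates the 85% threshold remains out of reach, so the study would still not be declared a success.

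This is a cheap improvement that should be made. It does not invalidate the design, and the sample size is unaffected.

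**What to change.** 1. Before the first chart review, fix a written concordance checklist. Draw it from the source guidelines and statements, not from the aid's output, since scoring against that output would favour the arm that was shown it.
2. Apply the checklist identically in both arms, including how recommendations that were offered but declined are documented and scored.
3. Give reviewers and committee members extracts containing the clinical data, orders and documented offers, with the arm and all references to the aid removed.
4. Make the foreseen committee definite, and send it every unclear chart from both arms.
5. Reword the vote: *consistent if at least 2 of 3 members independently rate the record consistent, otherwise inconsistent*.

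The cost is protocol wording and some coordinator time to prepare extracts. No extra patients are needed, and no assessors beyond the committee already foreseen. Masking will be imperfect where free text hints at the aid.

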### Exploratory endpoints

Overall favorability of the clinical decision aid will be evaluated using patient and physician focus group comments collated qualitatively. Cancer survivors and physicians will be asked to comment on particular features of the clinical decision aid that contribute to improving usability, understandability, and visual acceptability of the clinical decision aid. This will help us identify ways in which the clinical decision aid tool can be further improved for use by both patients and clinicians.

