### Statistical methods

#### Sample size and power analysis

Assuming 40% consistency with evidence-based recommendations at baseline for both groups [18, 20, 40], we will consider clinical significance at a 50% increase from baseline, which corresponds to 60% consistency with the recommendations. To go from 40% at baseline to 60% in the intervention arm of the trial (i.e., Clinical Decision Aid group) with 80% power requires 97 patients in each group, or 194 total patients. We may be powered to detect such a clinically reasonable change in the primary endpoint. Although we may be powered for this modest change, we could also consider a greater increase from baseline. To go from 40 to 85% with 80% power requires 17 patients in each group, or 34 total patients. We would also be powered for this, but this increase may not be reasonably obtainable.

In this feasibility study, the total number of patients will be limited to 200. One cohort of 100 patients will have clinic visits with current practice plus the clinical decision aid. The other cohort of 100 patients will have clinic visits with current practice alone. This should allow for capturing a variety of cancers and include ethnic minorities in each group.

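### The trial is sized for a rise in concordance from 40% to 60%, but success requires at least 85% in the aid group, so the stated 80% power does not apply to the success rule

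*Protocol article*

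**What the plan says.** Two sections of the protocol article's Methods set targets for the same outcome.

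Sample size and power analysis starts from "Assuming 40% consistency with evidence-based recommendations at baseline for both groups". It continues: "we will consider clinical significance at a 50% increase from baseline, which corresponds to 60% consistency with the recommendations". The sample size follows: "To go from 40% at baseline to 60% in the intervention arm of the trial" "with 80% power requires 97 patients in each group, or 194 total patients". Enrolment is capped at 200, 100 per arm. The section also considers a rise from 40% to 85%, for which it gives 17 per group, and comments: "We would also be powered for this, but this increase may not be reasonably obtainable".

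Primary endpoints states what determines success. At least "85% of clinic visits using the clinical decision aid resulting in pursuit of medication use and cardiac imaging surveillance patterns" must match recommendations for cancer survivors, "with overall rates the same or higher than the group without the clinical decision aid". Favourable survey responses and focus-group comments are also required, with no cut-off in that sentence.

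Focus-group findings are elsewhere classed as exploratory. The Focus groups section calls them part of an exploratory study, and Exploratory endpoints says: "Overall favorability of the clinical decision aid will be evaluated using patient and physician focus group comments collated qualitatively".

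**The concern.** The effect that justifies the sample size and the result that counts as success are different quantities. The power statement concerns a test of the difference between two arms. The success rule concerns an absolute level in one arm, set 25 percentage points above the sizing target (85 minus 60), plus a comparison of observed rates with no test and no minimum difference.

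A reader who sees 80% power will take it as the chance that the trial succeeds if the aid works as hoped. It is not. If the aid produces the gain that the article itself calls clinically significant, the success criterion is missed. The sponsor must then either report an unmet criterion beside a significant 20-point gain, or reinterpret the criterion after seeing the data. The article fixes both numbers, so this is not detail left to a fuller document.

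**Working it through.** **Inputs from the protocol article.** Control rate 40%, target 60%, 80% power, 97 per group, alternative rate 85% with 17 per group, and 100 per arm planned (Sample size and power analysis); significance at P < 0.05 (Data analysis); success at 85% or more of aid visits and not below control (Primary endpoints).

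**Assumptions.** The test is two-sided (the sample size section does not state sidedness). One visit is scored per patient, and visits are independent.

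**1. Reproduce the stated sample sizes.** Pooled formula without continuity correction:

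n = [1.96 × √(2p̄(1−p̄)) + 0.8416 × √(p1(1−p1) + p2(1−p2))]² / (p1 − p2)²

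- 40% vs 60%, p̄ = 0.50: (1.96 × 0.7071 + 0.8416 × 0.6928)² / 0.04 = 3.877 / 0.04 = 96.9, so 97. This matches.
- 40% vs 85%, p̄ = 0.625: (1.96 × 0.6847 + 0.8416 × 0.6062)² / 0.2025 = 3.430 / 0.2025 = 16.9, so 17. This matches.

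The stated sizes are therefore those of a two-sided between-arm test at 0.05. At 100 per arm, its power for 40% vs 60% is Φ[(0.20 × √100 − 1.386) / 0.6928] = Φ(0.886) = 0.81.

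**2. Chance of meeting the 85% threshold.** Exact binomial P(X ≥ 85) with n = 100:

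| True aid-group rate | Probability |
|---|---|
| 60% | 5.1e-8 |
| 70% | 0.0004 |
| 80% | 0.13 |
| 85% | 0.57 |
| 88% | 0.86 |
| 90% | 0.96 |

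At the sizing target, the test is significant about 81% of the time and the threshold is essentially never met.

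**3. Sensitivity at a true 60%.** The threshold counts visits and the sizing counts patients, so the number of visits was varied: 3.8e-8 with 97 visits, 1.2e-14 with 200, 3.4e-21 with 300. Clustering by physician (assumed intraclass correlation 0.05 to 0.20 and 3 to 10 physicians; the article gives neither) raises the chance to between about 3e-6 and 2%. The conclusion does not change.

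**4. Both numeric conditions with no true benefit.** P(X_aid ≥ 85 and X_aid ≥ X_control), 100 per arm, by exact enumeration:

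| True rate in both arms | Probability |
|---|---|
| 40% (planning value) | 2e-20 |
| 60% | 5e-8 |
| 80% | 0.12 |
| 85% | 0.43 |
| 90% | 0.55 |

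These figures leave out the survey and focus-group condition, which can only lower them.

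**The case against.** - **The higher bar may be deliberate.** This is a feasibility study. Sizing on a minimum worthwhile difference while hoping for more is a recognised choice, and 60% is a minimum rather than a forecast. A physician's offer counts as concordant even if the patient declines, and the aid displays the recommendations, so a high aid-group rate is not implausible; at a true 90% the threshold is met 96% of the time. This has some force. But the rule stands under Primary endpoints as what determines success, and the article itself doubts that 85% can be reached.
- **The 85% case was powered, at 17 per group.** That is power to detect a difference from 40%, not the chance of observing 85% or more, which is 0.57 even when 85% is the true rate.
- **Success is not the only analysis.** Data analysis plans between-group comparisons of medication use and imaging at P < 0.05. This stands. A reader might infer that the trial cannot show improvement, or that a significant gain would go unreported. The article does not support that: the gain would be reported beside an unmet criterion.
- **An ineffective aid could be declared successful.** A reader might infer this from the not-below-control condition. Under the plan's own 40% it does not happen: an aid group at 85% or more would be some 45 points above control. It becomes a real possibility only with control concordance of about 80% or more, twice the assumed rate.
- **Acceptability belongs in the decision.** The stated objective and the central hypothesis both include it. This stands, and the article gives no reason to strike focus-group comments from the success decision. Their exploratory label and their role in that decision do need to agree.

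**Conclusion.** The inconsistency is in the text and does not depend on fine assumptions. The stated 80% power belongs to the test of 40% against 60%, not to the success rule. At the sizing target, the chance of reaching 85% is about 5e-8 with 100 independent visits, and at most about 2% under the clustering scenarios tried; the between-arm test would be significant about 81% of the time.

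The weakness of the not-below-control condition is secondary and conditional. It matters only if true control concordance is about 80% or more, where the two numeric conditions are met without benefit 12% (80%), 43% (85%) or 55% (90%) of the time, before the survey and focus-group condition. It is not a risk at the planned 40%.

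**What to change.** - Define success on the primary concordance endpoint by the comparison the trial is sized for: the 95% confidence interval for the difference in concordance, aid minus control, in all randomised patients, lies above zero.
- Relabel 85% as a descriptive feasibility benchmark. Report the aid-group rate with its exact confidence interval, and state in advance the probability of meeting the benchmark over a range of true rates, as in the table above.
- Keep acceptability (surveys and focus groups) as a separate feasibility criterion if wanted, and make the exploratory label in Focus groups and Exploratory endpoints agree with the role given under Primary endpoints.

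The cost is wording in the protocol and analysis plan. No extra patients are needed: power is about 81% at 100 per arm. That assumes all 100 are evaluable and independent, and the margin over the required 97 is only three patients per arm.
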